11. AFP
12. HBV DNA (PCR fluorescent quantitation)

Ten mL blood sample from each screened patient will be required. The serum will be distributed into two vials (2 mL for each), and kept at minus 70 centigrade freezer for repeating assay at reference lab.

### Baseline visit (week 0), and vaccination

#### Baseline visit

After the patient’s medical history and informed consent have been obtained, the baseline physical examination (temperature, heart rate, and blood pressure) will be performed prior to randomization and vaccination. Patients who meet the eligibility requirements for enrollment will be assigned allocation number to patients in terms of the sequence of recruitment.

#### Vaccination

Study agents will be administrated to each patient according to the allocation number on the label of study agent.

Precaution

1. Products should be shaken thoroughly prior to administration;
2. Products should be inspected visually for particulate matter or discoloration prior to administration;
3. Epinephrine should be available for potential immediate allergic reactions;
4. Injection should be carried out by experienced and per-designated personnel;
5. All used study agent-related things including empty ampoules, packages and labels should be kept;
6. To ensure the accuracy of dosage, one mL syringe should be used for injection.

Study agent code will be assigned strictly to patient in terms of the recruitment sequence. All instruction on the label of study agent will be followed.

Administration

With thorough agitation, 1 mL (for either 30 g YIC group or 60 g YIC group) vaccine will be drawn from ampoule using 1 mL syringe, and will be injected to patient in the deltoid region. The injection will be given at day 1, week 4, 8, 12, 16 and 20.

With thorough agitation, 1 mL placebo will be drawn from ampoule using 1 mL syringe, and will be injected to patient in the deltoid region. The injection will be given at day 1, week 4, 8, 12, 16 and 20.

A total of 240 chronic hepatitis B patients will be recruited, and assigned to 30 g (group 2), 60 g YIC (group 3), and placebo group (group 1) in a ratio of 1:1:1.

The immediate reaction within 30 minutes after injection will be observed. Concurrently, basic medication (Silymarin and Hu Gan Tablet) will be distributed to each participated patient. To record the solicited and non-solicited reaction in the following 4 weeks after injection, diary card will be distributed. Corresponding instruction for filling in out will be given by investigator.

### Visits during the treatment period (Week 4, 8, 12, 16, and 20 ± 4 days after the initial dose)

During the treatment period, interview and physical examination (temperature, heart rate, and blood pressure) will be conducted at week 4, 8, 12, 16, 20 and 24. Concurrently, a serials test will be performed for each recruited patients, including liver function (ALT、AST、TBil、DBil、TP、ALB、and AKP), biochemical tests, blood cell count, microscopyd, uric testsd, renal function and assays for electrolytes.

Two vials of serum sample (2 mL for each) will only be required from each patient at week 12. The serum samples will be stored at minus 70 centigrade freezer for virologic response testing at reference lab at the end of study.

The same study agent will be administrated to each patient once every four weeks till week 20. The immediate reaction within 30 minutes after injection will be observed at research centers. A diary card to record the solicited and non-solicited reaction in the following 4 weeks after each injection will be distributed to patient with the basic medication. The diary card from the pervious vaccination will be collected at the beginning of each injection.

### Visits at the end of treatment (Week 24  4 days）

At the end of treatment, except for the physical examination (temperature, heart rate, and blood pressure) and all tests described above, AFP will be tested when it is necessary.

The diary card for the injection at week 20 will be collected from each patient. Ten mL blood sample will be collected and separated into 2 vials (2 mL per vial). Serum sample will be kept at minus 70 centigrade freezer for virologic response testing at reference lab in the end of study.

### Visit at the end of basic treatment and follow-up（Week 36/44  4 days）

Twice visits will be conducted at week 36 and 44 during the follow-up period. Following procedures will take place during each interview:

1. Physical examination (temperature, heart rate, and blood pressure）;
2. Liver function, including ALT、AST、TBil、DBil、TP、ALB、AKP;
3. Biochemistry tests, including blood cell count, microscopyd, uric testsd, renal function and electrolytes;
4. AFP when it is needed;
5. Collect 2 vials serum sample (2 mL for each) and keep at minus 70 centigrade freezer for virologic response testing at reference lab at the end of study;
6. Collect and distribute diary card to record serious adverse event between two visits.

### Blinding and Unblinding

#### Blinding

This is a double blind (with in-house blinding) clinical trial. Study blinding is necessary to ensure the integrity of the data being collected. However, study blinding must not compromise the safety of the patients participating in the trial. The patient, investigator, and clinical personnel monitoring the study data are blinded to the study agent (30 μg YIC, 60 μg YIC and placebo). All personnel including the SPONSOR and the internal and external personnel working with the SPONSOR will remain blinded to the study agent assignment of each patient until the completion of the study.

#### Emergency unblinding

A sealed envelope which contains the individual randomization information for each randomized patient prepared by the independent biostatistician will be distributed with study agents to corresponding study centers. The envelope must be kept by pre-designated co-investigator at each center. Except in the case of medical necessity, such as serious adverse events, a patient’s treatment should not be unblended without the approval of co-principle investigator. The sealed envelope should be used ONLY if absolutely essential for the welfare of the patient.

If any patient is unblinded prior to completion of the study, the investigator must promptly contact the CRO, and document the circumstances on the envelope and sign the name of the person who unblinds the treatment. Once the unblinding occurs, the unblinded patient will be classified to lost-to-follow-up. The disclosure or masked envelopes held by the co-investigator at each center will be collected at the end of the study to ensure that the unblinding was properly documented. The sealed envelopes must be checked by clinical monitor at each visit.

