### Discontinuation/Withdrawal

Any patient who had signed a consent form, and meet the following criteria will be defined as premature withdrawal.

1. Patients who request to quit themselves;
2. Patients who violate the study protocol;
3. Patients who become pregnancy;
4. Patients who are unblinded due to SAE;
5. Patientsduring the treatment period who developed the following symptoms
   - - - Hepatic cirrhosis
       - Hepatic failure
       - And hepatoma.

If the withdrawal occurs due to the adverse events or abnormal laboratory tests, details should be recorded in the CRFs.

- 1. Laboratory assay

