### Recording and reporting of SAE

The investigator is responsible for the detection and documentation of events meeting the criteria and definition of a serious adverse event (SAE) as provided in this protocol. Each patient will be instructed to contact the investigator immediately should the subject manifest any signs or symptoms they perceive as serious.

SAEs will be reported concurrently to CRO, SPONSOR, Principle Investigator, IRB, and SFDA within 24 hours, once the investigator determines that the event meets the protocol definition of a SAE. The SAE Form will always be completed as thoroughly as possible with all available details of the event, signed by the investigator (or designee), and will always provide an assessment of causality at the time of the initial report.

After the initial SAE report, the investigator is required toactively follow each subject and provide further information to the CRO, SPONSOR, Principle Investigator, IRB, and SFDA on the subject’s condition. Investigators will follow-up subjects with SAEs until the event has: resolved or subsided or stabilized or disappeared or the event is otherwise explained, or the subject is lost to follow-up.

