# Statistical Methods

All data will be double entered into custom-made data entry programs. The data management programs include range and consistency checks. An SAS program (SAS Institute Inc., Cary, NC, USA ) will be applied for statistical analysis.

- 1. Safety

The safety analysis will be performed based on the safety set (SS). It will include patients who received at least one injection, and completed at least one interview of safety evaluation after injection.

Three-wise comparison employed the chi square test, or Fisher’s exact test when data were sparse, for dichotomous outcomes will be performed to test the difference of occurrence of adverse events among placebo, 30 μg YIC and 60 μg YIC groups. A p-value < 0.05 (two-tailed) will be considered statistically significant.

- 1. Efficacy

The efficacy analysis will be conducted based on both full analysis and per-protocol sets. For full analysis set (FAS), it will include patients who were randomized, received at least one injection, and completed at least one interview of efficacy evaluation after injection. The intent-to-treat principle will be applied for the dataset. For per protocol set (PPS), it will include patients who met following three conditions：

1. Baseline information are available；
2. Complete full course of treatment and follow-up without protocol violation；
3. With good compliance (between 80% and 120%）.

For those important indicators, the missing data will be estimated using the most previous observation (LOCF, last observation carry forwards).

The primary efficacy hypotheses will be tested for response rate of primary endpoint in 30 μg YIC or/and 60 μg YIC groups > that in placebo group (2-tailed). The Chi square test, or Fisher’s exact test when data were sparse, will be employed. A p-value, point estimate, as well as confidence interval will be calculated.

The secondary efficacy outcomes will be summarized in a similar fashion.

Repeated measures analysis will be performed using a generalized estimating equations (GEEs) method to adjust the dependence among repeated observations made on the same patient while testing the group and time effects. A p-value < 0.05 (two-tailed) will be considered statistically significant.

- 1. Sample size

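### Labelling an emergency-unblinded patient as lost to follow-up can end follow-up of the SAE behind the unblinding and makes obtainable efficacy outcomes missing; separately, the safety set may omit an injected patient with no later visit

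*Protocol*

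**What the plan says.** **Unblinding.** Protocol section 4.3.7 (Emergency unblinding) reserves the sealed envelope for the patient's welfare and names the typical reason: "Except in the case of medical necessity, such as serious adverse events, a patient’s treatment should not be unblended without the approval of co-principle investigator". It then fixes the consequence for any patient unblinded before the study ends: "Once the unblinding occurs, the unblinded patient will be classified to lost-to-follow-up".

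**Withdrawal.** Section 4.3.8 lists, among premature withdrawals, "Patients who are unblinded due to SAE". It adds: "If the withdrawal occurs due to the adverse events or abnormal laboratory tests, details should be recorded in the CRFs".

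**Follow-up of events.** Section 4.5.7 has every adverse event followed until it has resolved, stabilised or been explained. Section 4.5.10 gives the same end points for SAEs and adds one more: "or the subject is lost to follow-up".

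**Analysis sets.** Section 6.1 defines the safety set: "It will include patients who received at least one injection, and completed at least one interview of safety evaluation after injection". Section 6.2 requires, for the full analysis set (FAS), randomisation, one injection and one post-injection efficacy interview, and says "The intent-to-treat principle will be applied for the dataset". Missing values of important indicators are filled by last observation carried forward (LOCF).

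**The concern.** Loss to follow-up normally describes a patient who can no longer be reached. Here it is assigned by rule to a patient who has just had a medical emergency and is normally in the investigator's care. The protocol attaches two consequences to such a label.

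First, it meets a stopping condition for SAE follow-up. The outcome and final causality of the events that matter most in a phase IIB vaccine trial could then go unrecorded.

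Second, it turns obtainable virology into missing data. The trigger is harm, which may differ by arm: section 10.5.1 names local reactions, arthralgia, erythra and temporary ALT elevation after the vaccine. Missing data that arise this way are unlikely to be unrelated to treatment, and they weaken an analysis meant to follow intent-to-treat.

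The safety-set condition raises a related but separate problem. A requirement to have come back can remove a patient whose reaction was the reason for not coming back.

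**Working it through.** The protocol has no figure on this point to reproduce, so the main check sets the sections side by side.

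**Step 1: status and follow-up of a patient unblinded for an SAE.**

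| Section | Status or rule | Does SAE follow-up continue? |
|---|---|---|
| 4.3.7 | Lost to follow-up | Not stated |
| 4.3.8, item 4 | Premature withdrawal; event details go in the CRF | Not stated |
| 4.5.7 | All adverse events followed to resolution, stabilisation or explanation | Yes, with no exit for loss to follow-up |
| 4.5.10 | As 4.5.7, or until the subject is lost to follow-up | No, once the 4.3.7 label applies |

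An investigator who applies 4.3.7 and then 4.5.10 may stop. One who applies 4.5.7 may not. The protocol does not say which section prevails.

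**Step 2: efficacy data.** Efficacy rests on HBV DNA, HBeAg and anti-HBe (section 4.6). Samples for these are taken at screening and at weeks 12, 24, 36 and 44, and response is assessed at weeks 24 and 44. If sampling stops at unblinding:

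- Before week 12: there is no post-baseline virology, so the patient may fail the FAS condition of one post-injection efficacy interview.
- From week 12 to before week 24: the week 12 result stands in for both weeks 24 and 44 under LOCF.
- From week 24 to before week 44: the last result available (week 24 or 36) stands in for week 44.

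In each case the later blood could have been drawn, since the patient is normally still reachable.

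**Step 3: safety set.** The synopsis uses "interview" for scheduled visits, and the first after an injection is week 4. Section 4.5.2 calls the 30-minute check an observation. On that reading, a patient with an immediate reaction to the first injection who never returns leaves both numerator and denominator. If the 30-minute observation counts as the interview, almost no injected patient is dropped. The protocol does not settle which is meant.

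**Step 4: possible size.** With 240 patients in a 1:1:1 ratio there are 80 per arm, and one patient is 1/80 = 1.25 percentage points. The protocol gives no severe-reaction rate, so the counts below are assumed. They apply only to patients dropped for want of a later interview. The test is Fisher's exact, two-sided, against 0/80 on placebo.

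| Severe reactions in a vaccine arm | Dropped from set | Analysed as | p |
|---|---|---|---|
| 6 | 0 | 6/80 | 0.028 |
| 6 | 1 | 5/79 | 0.028 |
| 6 | 2 | 4/78 | 0.057 |
| 6 | 3 | 3/77 | 0.12 |
| 7 | 0 | 7/80 | 0.014 |
| 7 | 3 | 4/77 | 0.056 |

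Under these assumptions, losing one patient does not move the p-value, while losing two or three can take it past 0.05.

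**The case against.** A reader might infer that the patients with the worst reactions leave the data by rule. The protocol does not support that. No section removes unblinded or lost-to-follow-up patients from the safety set or the FAS. All adverse events go on the adverse event forms (4.5.3), SAEs are reported within 24 hours with a causality assessment (4.5.10), and details of withdrawals for adverse events go in the CRF (4.3.8). A patient unblinded after one post-injection safety interview stays in the safety set with the event counted. What is at risk is what follows the unblinding, plus injected patients with no later interview.

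A reader might also infer that section 4.3.8 contradicts intent-to-treat because it lists "Patients who violate the study protocol" as premature withdrawals. It does not: section 6.2 excludes violators from the per-protocol set only. The lost-to-follow-up label likewise weakens the intent-to-treat analysis rather than contradicting it.

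Nor do the documents show that one such patient would decide the efficacy result. At the planned 20% against 3% (section 6.3), 80 per arm gives 16 responders against about 2, p = 0.0007. Counting one vaccine responder as a non-responder (15/80) gives p = 0.0014; excluding one (15/79) gives p = 0.0007.

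Frequency also tells against a large effect. Envelopes are for essential use only, phase IIa saw no SAE, and almost all its adverse events were mild. Requiring one post-dose safety evaluation is a common convention, and the 30-minute observation may satisfy it.

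All of this stands and limits the point. It does not remove the conflict over SAE follow-up or the avoidable loss of later outcomes.

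**Conclusion.** The concern holds in a limited form. As written, sections 4.3.7 and 4.5.10 together allow follow-up of an SAE to stop because the blind was broken for it. That conflicts with section 4.5.7, and section 4.3.8 assigns a different status. This part rests on the text alone.

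The efficacy consequence assumes that the label ends scheduled sampling, which its ordinary meaning implies but the protocol does not spell out. Outcomes at weeks 24 and 44 are then carried forward, or the patient may miss the FAS if unblinded before week 12.

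The safety-set gap depends on reading the interview as a scheduled visit. Synopsis usage favours that reading, but the definition does not fix it.

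The number of patients affected cannot be estimated from the protocol and is probably small. The case for acting is that the lost information concerns serious events and is cheap to keep, not that a particular result is shown to change.

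**What to change.** 1. In section 4.3.7, delete the classification of unblinded patients as lost to follow-up.
2. Reconcile sections 4.3.7, 4.3.8 (item 4), 4.5.7 and 4.5.10 so that an unblinded patient has one status and SAE follow-up continues after unblinding. Changing 4.3.7 alone would leave item 4 of 4.3.8 in conflict.
3. State that unblinded patients stay on the scheduled visits and serum samples unless consent is withdrawn, and are analysed in the FAS in their randomised arm.
4. In section 6.1, define the safety set as all patients who received at least one injection.

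Whether injections continue after unblinding is a clinical matter and is not addressed here.

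The cost is protocol wording plus visits and samples already on the schedule. The downside is that a few unblinded patients remain in the FAS. Their outcomes are reference-laboratory assays run after the 44-week follow-up, so knowledge of treatment should have little effect on the measurement.

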#### Endpoint unblinding

All patients who completed the full treatment will be unblinded at the end of follow-up (Week 44). Two-step unblinding method will be applied. After data freezing, the patients will be classified to group A, B and C for safety and efficacy endpoint analysis. When safety and efficacy of each group are derived, the assignment of group A, B and C will be given.

### Discontinuation/Withdrawal

Any patient who had signed a consent form, and meet the following criteria will be defined as premature withdrawal.

1. Patients who request to quit themselves;
2. Patients who violate the study protocol;
3. Patients who become pregnancy;
4. Patients who are unblinded due to SAE;
5. Patientsduring the treatment period who developed the following symptoms
   - - - Hepatic cirrhosis
       - Hepatic failure
       - And hepatoma.

If the withdrawal occurs due to the adverse events or abnormal laboratory tests, details should be recorded in the CRFs.

- 1. Laboratory assay

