### Treatment and follow-up of adverse events

Any adverse event must be treated with acceptable method. Investigators must report and discuss with SPONSOR when a method repelling with study agent has to be implemented, since this activity will cause premature withdrawal. All adverse events should be followed-up until the event has: resolved or subsided or stabilized or disappeared or the event is otherwise explained.

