### Unscheduled pregnancy

Any pregnancies which occur during study period should be reported to corresponding investigator, and all study related-treatment should be stopped consequently. Investigator should report to both CRO and SPONSOR using specific-pregnancy form. The pregnant patient should be followed-up till delivery, the outcome of pregnancy and delivery should be reported to both CRO and SPONSOR. The pregnancy occurs with participant’s wife also should be reported and followed.

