### Secondary endpoint

The secondary endpoint was designated as both HBeAg seroconversion and suppression of HBV DNA.

- 1. Basic treatment

Considering the ethical issue, each patient who participates in this trial will be given basic treatment besides of study agents throughout 44-week study period as following:

- 1. Silymarin, 50 mg/tablets, 3 tablets per time, tid；
  2. Hu Gan Tablet, 0.36g per tablet, 4 tablets per time, tid.
  3. Concomitant medication

Concomitant medication is defined as: any vaccine, any other medication relevant to the protocol and administrated during the period starting from prior to treatment until the end of follow-up.

At each study center, the investigator should question the patient about any medication taken between two injections. All concomitant medication must be recorded in the CRFs with the trade name, generic name, indication, dose, route of administration, start and end dates of treatment.

The flowing drugs, treatments and behaviours are not allowed:

- 1. Any immunosuppressive or immunostimulant therapy, anti-viral therapy, drugs that have effects on decreasing the level of ALT, androgenic drugs, steroids, contraceptive drugs;
  2. Any investigational or non-registered anti-HBV drug, herbs or other patient self-chozen therapies
  3. Usage of acetaminophen more than 4 g per day;
  4. Intake of spirits more than 20 g per day;

1. Data management

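### Section 4.3.8 makes every protocol violator a premature withdrawal, and nothing in the protocol keeps withdrawn patients in efficacy sampling, so week 24 and 44 readings can be lost without need

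*Protocol*

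**What the plan says.** Protocol section 4.3.8 opens with a definition: "Any patient who had signed a consent form, and meet the following criteria will be defined as premature withdrawal". Item 2 of its list reads "Patients who violate the study protocol". It has no major/minor grading and no room for investigator judgement. The only procedure attached is a CRF entry when the withdrawal is due to an adverse event or an abnormal laboratory test.

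Other sections bear on what withdrawal means:

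- 4.3.7, on emergency unblinding: "Once the unblinding occurs, the unblinded patient will be classified to lost-to-follow-up". Unblinding due to an SAE is also item 4 of the 4.3.8 list.
- 4.5.7, on adverse events that need a treatment incompatible with the study agent: the sponsor must be consulted, "since this activity will cause premature withdrawal".
- 4.5.11 gives stopping treatment and withdrawal as separate examples of notable events.
- 4.8 lists what is not allowed. It runs from "Any immunosuppressive or immunostimulant therapy, anti-viral therapy" to "Intake of spirits more than 20 g per day".

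For efficacy serum during the injection period, 4.3.4 says: "Two vials of serum sample (2 mL for each) will only be required from each patient at week 12". Sections 4.3.5 and 4.3.6 add weeks 24, 36 and 44. The primary endpoint is assessed at weeks 24 and 44 (4.6.1). Section 6.2 applies intent-to-treat to the FAS, requires at least one efficacy evaluation after injection for entry to the FAS, fills gaps by LOCF, and limits the PPS to patients who completed treatment and follow-up without violation.

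**The concern.** The rule ties a matter of conduct to a patient's status in the study. Taken literally, drinking above the 4.8 limit has the same consequence as taking an antiviral. If that status ends sampling, the protocol itself creates missing primary-endpoint data after randomisation, for patients who have not withdrawn consent.

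The replacement value is poor. A week 12 sample follows at most four of the six injections, whereas the rationale in 2.1 says that responses to immunotherapy need to be looked for some time after the last one. If withdrawals differ between arms in number or in type of patient, the randomised comparison is disturbed. Serum that was never drawn cannot be recovered by an analysis plan, so this has to be settled in the protocol.

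**Working it through.** **Step 1. Does withdrawal mean leaving the study?** No section says so outright. Three places point that way. 4.3.7 turns unblinded patients into losses to follow-up. 4.5.7 treats premature withdrawal as a consequence serious enough to discuss with the sponsor first. 4.5.11 lists withdrawal apart from stopping treatment.

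**Step 2. Does any section keep withdrawn patients in efficacy sampling?** The candidates are:

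| Place | Covers | Requires efficacy serum after withdrawal? |
|---|---|---|
| Synopsis, study procedure | Assay of all patients' samples at the reference laboratory | No, it concerns assay of samples |
| 4.3.4 to 4.3.6 | Schedule of draws | Silent on withdrawn patients |
| 4.4.3 | Liver, renal, electrolyte, blood count and urine tests for all enrolled patients | No, site safety tests only |
| 4.5.7, 4.5.10 | Follow-up of adverse events and SAEs | No |
| 4.5.9 | Pregnancy: "The pregnant patient should be followed-up till delivery" | No, pregnancy outcome only |
| 6.2 | FAS under intent-to-treat | No, an analysis set creates no observation |

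**Step 3. What is lost if withdrawal ends sampling?** Efficacy rests on HBV DNA, HBeAg and HBeAb (4.6), with post-baseline serum at weeks 12, 24, 36 and 44 only.

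- Before week 12: there is no post-baseline virology, so the FAS entry condition is not met.
- From week 12 to before week 24: both endpoint readings are carried forward from week 12. Injections fall on day 1 and weeks 4, 8, 12, 16 and 20, so that sample follows at most four of six.
- From week 24: week 24 is observed. Week 44 is carried forward from week 24 or week 36.

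**Step 4. Scale, as an illustration.** Inputs from 6.3: 78 per arm, 20% dropout, 80% power, 0.05 level, response 35% (60 µg), 20% (30 µg) and 3% (placebo). The test is two-sided (6.2).

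The plan's own figure reproduces. For 20% vs 3%, the continuity-corrected formula gives 66 per arm, and 66 × 1.2 = 79.2, or 80, within 2 of 78. As a cross-check, 78 × 0.8 ≈ 62 evaluable per arm gives exact Fisher power of 81.9%.

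The documents give no violation rate. Assume that x of 78 patients in each arm are withdrawn and carried forward as non-responders. The observed rate is p × (78 − x)/78, and differences shrink by the same factor.

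| x | Factor | 17-point difference (20% vs 3%) | 32-point difference (35% vs 3%) | Power, 20% vs 3%, chi-square / Fisher |
|---|---|---|---|---|
| 0 | 1 | 17.0 | 32.0 | 95.2% / 91.9% |
| 4 | 74/78 | 16.1 | 30.4 | 94.0% / 89.9% |
| 8 | 70/78 | 15.3 | 28.7 | 92.7% / 87.6% |
| 16 | 62/78 | 13.5 | 25.4 | 89.1% / 81.5% |

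The last row is the full 20% allowance. If those 16 leave the analysis instead (62 per arm, 20% vs 3%), power is 89.4% / 81.9%. Power for 35% vs 3% is at least 99.8% throughout.

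**Step 5. The opposite risk.** Keeping placebo patients who took a barred antiviral, at their observed outcome, raises the placebo rate. Section 2.1 gives 20-25% HBeAg loss after one year of lamivudine. With x such patients the rate is ((78 − x) × 0.03 + x × r)/78:

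- x = 4, r = 0.20: (2.22 + 0.80)/78 = 3.9%
- x = 8, r = 0.25: (2.10 + 2.00)/78 = 5.3%

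That is a shift of 0.9 to 2.3 points, of the same order as the 0.9 to 1.7 points lost from the 17-point difference at x = 4 to 8. Exposure in this trial would be shorter than a year, but HBV DNA suppression also counts as response and the protocol gives no figure for it.

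**The case against.** The strongest reply is that 4.3.8 only classifies. It does not say that visits or serum stop, and several places lean towards continued contact: the synopsis plans virology for all patients, 4.4.3 runs site tests on all enrolled patients to week 44, 4.5.7 follows adverse events to resolution, and 6.2 removes violators only from the PPS. The separation of withdrawal from stopping treatment in 4.5.11 is a list of examples, not a definition. This stands to the extent that the protocol does not order sampling to end. It does not remove the point, because none of these places requires efficacy serum after withdrawal, and a centre following the likelier reading would stop drawing it.

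Four stronger readings are tempting and are not supported:

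- **That the protocol expressly ends sampling for violators.** It is silent.
- **That violators alone are left without a follow-up rule.** The pregnancy provision says nothing about scheduled visits or efficacy serum either, so the gap covers the other reasons on the list too.
- **That a visit outside the 4-day window triggers withdrawal.** No section calls a late visit a protocol violation. Grading of violations may also sit in a statistical analysis plan that is not shown.
- **That the trial loses its planned power.** Step 4 shows otherwise. Its assumption is harsher than the likely effect, since patients withdrawn after week 24 keep that reading and a week 12 value need not be a non-response.

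**Conclusion.** The point holds as a protocol rule that is fixed badly. It lets primary-endpoint readings be lost after randomisation for reasons other than consent, against the intent-to-treat principle in 6.2, and without benefit to the PPS. It rests on one inference, that centres will take withdrawal to mean leaving the study. The wording elsewhere makes that likely but not certain.

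The size and direction of any bias cannot be derived from the documents. The shrinkage of 0.9 to 3.5 points in the 17-point difference depends on an assumed violation rate, equal across arms, and on counting every withdrawn patient as a non-responder. The stated 80% power is not in question. This is an inexpensive improvement that should be made, not a flaw that invalidates the design.

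**What to change.** Amend 4.3.8 so that a protocol violation, like the other non-consent reasons on the list, leads at most to stopping study injections. The patient then continues the scheduled visits and serum at weeks 12, 24, 36 and 44 unless consent is withdrawn, is analysed in the FAS as randomised, and is excluded only from the PPS. Align 4.5.7 (adverse events treated with an incompatible method), and replace the loss-to-follow-up status of unblinded patients in 4.3.7. Record any barred antiviral with its dates.

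The cost is amendment wording and at most four already scheduled draws per affected patient. The downside is that outcomes after a barred antiviral are harder to interpret. Counting them as non-response or as observed is a trade-off (step 5) that the documents do not settle. Recording the dates keeps both options open.
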